### Study objectives

The primary objective of this study is to evaluate effectiveness of day-case stapes surgery compared to in-hospital stapes surgery followed by one-day hospital admittance for otosclerosis, in terms of hearing improvement. In addition, subjective participants’ perception on hearing improvement, QoL, tinnitus, vertigo and cost-effectiveness will be assessed.

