### Sample size calculation and recruitment

To establish equivalence in postoperative mean air conduction of 5 dB (standard deviation 10) between the day-case and the inpatient group with an alpha of 0.05 and a power of 80 %, 51 participants per group are needed. To anticipate on a withdrawal of 10 % of the participants, 5 more participants than needed will be recruited per group. At the ENT department in UMC Utrecht, we perform an average of 80 (revision) stapedotomies per year. Assuming a participation rate of 75 %, we will be able to include the necessary number of 112 patients in two years. If participants wish to leave the study or the investigator decides to withdraw a participant from the study for urgent medical reasons, these participants will not be replaced unless these account for more than 10 %.

Patients will be recruited from the outpatient ENT department of the UMC Utrecht. If an otosclerosis patient meets the criteria for stapes surgery and the inclusion criteria for this study, one of the researchers will explain the content of the study and provide the patient with written patient information and an informed consent form. Patients consent to the use of their data for the research purposes outlined in this protocol, which includes publication of the results once the trial has been completed. Further details can be found in Additional file 1 (informed consent form; translated to English, original in Dutch). Patients that do not want to be included in the study because they want to undergo stapes surgery in a clinical setting will be asked whether they want to fulfill the study procedures and whether their data can be used for analysis.

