### Randomization, blinding and treatment allocation

A web-based randomization program (Julius Center, UMC Utrecht, Utrecht, The Netherlands) shall be used to allocate subjects randomly into two groups with stratification for age. Block randomization will be used with an allocation ratio of 1:1. The randomization chart, including block size, is established before the start of the study by an independent data manager and will not be available to any of the people involved with enrolment or treatment of participants. Consequently, treatment allocation sequence is concealed for participants, care providers and researchers. Blinding of both participants and care providers is not possible, since both participants and care providers will be aware of the surgical setting and hospital stay.

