### Pure-tone and speech audiometry

Pure-tone and speech audiometry will be performed preoperatively and at approximately two and twelve months postoperatively. Measurements will include mean four-frequency bone conduction thresholds, air conduction thresholds and air-bone gap. The following frequencies will be used to calculate mean thresholds: 500, 1000, 2000 and 4000 Hz. Sensorineural hearing loss will be evaluated using frequencies 1000, 2000 and 4000 Hz. Sensorineural hearing loss is defined as a deterioration in mean bone conduction thresholds exceeding 10 to 15 dB.

Performance on speech audiometry will provide information on word recognition abilities and can, in conjunction with pure-tone audiometry, help determine the degree and type of hearing loss.

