### Statistical analysis

Baseline characteristics per group will be described as means and standard deviations. Differences in the baseline will be analyzed using the independent samples students *t-*test or non-parametric tests for continuous variables and the Fisher’s exact test for categorical variables.

The primary and secondary outcome data are quantitative and will be presented both continuous and categorical. Between-group mean differences, rate differences and rate ratios with 95 % confidence intervals will be calculated. For further analysis of between-group differences in both primary and secondary outcomes the independent samples students *t–*test or non-parametric tests will be used for continuous outcomes and the Fisher’s exact test for categorical outcomes. Within-subject comparisons will entail differences in mean values and percentages before and after stapes surgery. These will be analyzed using paired *t*-tests for continuous measures and the McNemar test for categorical outcomes.

Missing values will be handled using multiple imputation and all analyses will be performed on an intention-to-treat basis. A sensitivity analysis will be performed using all of the data acquired from patients that opted not to be included in the study, but did fill out the questionnaires and underwent pure-tone audiometric and speech audiometric follow-up.

The data will be reported according to the CONSORT Statement [37, 38].

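### The between-arm comparison of air conduction is valid but unadjusted, giving up precision that preoperative audiometry and the age stratum could supply

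*Protocol article*

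**What the plan says.** The Statistical analysis section of the protocol article applies one rule to primary and secondary outcomes alike. Between-group differences get 95% confidence intervals and are then tested by an independent-samples t-test "or non-parametric tests will be used for continuous outcomes". No covariate-adjusted model is named anywhere.

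The data for adjustment are planned. "Pure-tone and speech audiometry will be performed preoperatively and at approximately two and twelve months postoperatively", and the mean thresholds use 500, 1000, 2000 and 4000 Hz, the frequencies of the primary outcome. The randomisation program will "allocate subjects randomly into two groups with stratification for age". Both primary and revision stapedotomies are eligible.

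Preoperative values are used in two places only. One is a comparison of the arms at baseline: "Differences in the baseline will be analyzed using the independent samples students" t-test or non-parametric tests, with Fisher's exact test for categorical variables. The other is the within-subject comparison before and after surgery, by paired t-tests and the McNemar test.

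The sample size section states the aim: "To establish equivalence in postoperative mean air conduction of 5 dB", with "standard deviation 10) between the day-case and the inpatient group", "with an alpha of 0.05" and 80% power, giving 51 per group.

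**The concern.** Neither use of the preoperative values adjusts the between-arm difference. The baseline tests may flag an imbalance but leave the estimate as it was, and the paired tests describe change over time, not the contrast between arms.

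This matters because an equivalence conclusion depends on the width of the interval. The whole interval has to lie within ±5 dB, so each decibel of half-width comes directly off the room left for the point estimate. Any outcome variation that is predictable from the preoperative threshold currently stays in the standard error, and a chance difference between arms in starting level carries over into the estimate.

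The article names its tests for the primary outcome, so this is a stated choice and not a detail left to a statistical analysis plan.

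**Working it through.** **Inputs from the protocol article.** Margin 5 dB, SD 10 dB, alpha 0.05 (sidedness not stated), power 80%, 51 per group (Sample size calculation and recruitment); 1:1 allocation (Randomization, blinding and treatment allocation); 95% intervals (Statistical analysis).

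**Assumptions.** The true difference is zero. The correlation r between preoperative and postoperative air conduction is not given, so a range is shown. The SD of 10 dB is read as that of the unadjusted postoperative value, since no residual SD or correlation is mentioned with it.

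**Step 1: reproduce the stated 51.** The one-sided two-sample formula is n = 2 × [(z₀.₉₅ + z₀.₈₀) × SD / margin]² = 2 × [(1.645 + 0.842) × 10 / 5]² ≈ 49.5, hence 50, or 51 with the t distribution. The figure therefore reproduces as a one-sided calculation with beta not split over two margins. For equivalence at a true difference of zero, z₀.₈₀ is replaced by z₀.₉₀. That gives 69 per group for a 90% interval (70 exact) and 85 for a 95% interval (86 exact).

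**Step 2: the unadjusted interval at 51 per group.** SE = 10 × √(2/51) = 1.98 dB. The half-width of the 95% interval is 1.984 × 1.98 = 3.93 dB. The observed difference must then lie within 5 − 3.93 = 1.07 dB of zero, which has a probability of about 41%. For a 90% interval the half-width is 1.660 × 1.98 = 3.29 dB, the room is 1.71 dB and the probability is about 61%.

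**Step 3: the adjusted interval.** Under ANCOVA the residual SD is 10 × √(1 − r²). Exact two one-sided test power at 51 per group:

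| r (assumed) | Residual SD, dB | Power, 95% interval | Power, 90% interval |
|---|---|---|---|
| 0 (unadjusted) | 10.0 | 41% | 61% |
| 0.2 | 9.8 | 45% | 64% |
| 0.3 | 9.5 | 49% | 67% |
| 0.5 | 8.7 | 65% | 79% |
| 0.7 | 7.1 | 88% | 94% |

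Taking off three degrees of freedom for the covariates changes these powers by no more than 0.1 percentage point. Power of 80% at 51 per group needs r of about 0.64 with the planned 95% interval, or about 0.52 with a 90% interval.

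**Step 4: chance imbalance.** Given a baseline difference d and equal SDs before and after surgery, the unadjusted estimate is expected to move by r × d. For d = 3 dB and r = 0.5 this is 1.5 dB, more than the 1.07 dB of room in Step 2. If the preoperative SD is also 10 dB (an assumption), 3 dB is 3 / 1.98 ≈ 1.5 standard errors, and an imbalance at least that large in either direction has a probability of about 13%.

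**The case against.** The strongest reply is that nothing in the named analysis is invalid, and that is right. Several stronger readings are tempting but not supported.

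- A reader might infer that the unadjusted estimate is biased. Over randomisations it is not, and chance imbalance is already part of its standard error. The 1.5 dB is a shift given one particular imbalance.
- A reader might infer that ignoring the age stratum makes a false claim of equivalence more likely. Omitting a prognostic stratification factor makes the standard error too large, so the error is on the cautious side. The documents give no association between age and outcome, and the effect may be negligible.
- A reader might see a conflict between an objective framed "in terms of hearing improvement" and an outcome that is the postoperative level. In a randomised comparison, the differences in postoperative level, in change and from ANCOVA all target the same treatment effect, so this adds no error.
- A reader might infer that adjustment restores the stated 80% power. That depends on an unknown r. Eligibility limits on the air-bone gap and on perceptive loss may narrow the preoperative range, and surgery is meant to remove the conductive component, so a correlation of 0.5 or more cannot be presumed. At r = 0.2 the gain is only about 3 to 4 percentage points.

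The shortfall in power itself comes from the sample-size formula, a separate matter that adjustment can offset but not correct. It is also fair that a journal article condenses a fuller protocol. That helps little here, because the article does name the tests.

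**Conclusion.** The point stands as one of lost precision. The plan specifies a valid, conservative comparison that leaves out the preoperative value of its own primary outcome and its own stratification factor. The gain from adjustment, in power to place the 95% interval within ±5 dB, is about 8 percentage points at r = 0.3, 24 at r = 0.5 and 47 at r = 0.7. It rests on an SD of 10 dB, 51 analysed per group, a true difference of zero and an assumed r. The omission is certain; the size of the benefit is not. The change should be made, but the planned analysis would not be wrong without it.

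**What to change.** For the primary outcome, replace the t-test or non-parametric test with a prespecified ANCOVA of postoperative four-frequency air conduction on treatment, preoperative air conduction, age stratum and primary versus revision surgery. Fit it at each of the two time points named for the primary outcome, about two and about twelve months, with no optional covariates. Judge the adjusted mean difference and its confidence interval against ±5 dB.

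Use the same model, with the preoperative score as covariate, for questionnaires that have a meaningful preoperative score. This excludes the Glasgow Benefit Inventory, which measures change as a result of surgery.

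The cost is a few degrees of freedom and slightly more analysis work. Preoperative audiometry and the age stratum are already part of the plan, and whether the operation is primary or revision is known for each patient. The trial is unblinded and described as still recruiting, so the model should be fixed before outcomes are compared. Deleting the baseline significance tests is optional and changes no result. The sample-size calculation needs its own correction.

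### The planned sensitivity analysis brings in never-randomised patients who can join only the inpatient side, so it cannot serve as a robustness check; the primary randomised analysis is not affected

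*Protocol article*

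**What the plan says.** Two sections of the protocol article have to be read together.

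- **Sample size calculation and recruitment.** Patients who decline "because they want to undergo stapes surgery in a clinical setting" are asked to complete the study procedures and to allow their data to be analysed. No such arrangement is described for people who decline for other reasons, and no day-case preference group is described. The Background states that stapes surgery in this clinic currently involves an overnight stay, so the setting these patients want is evidently the inpatient one.
- **Statistical analysis.** "A sensitivity analysis will be performed using all of the data acquired from patients that opted not to be included in the study", provided they completed the questionnaires and audiometric follow-up. The sentence before it puts all analyses on an intention-to-treat basis, with multiple imputation for missing values. The between-group tests named are unadjusted: t-test or non-parametric tests, and Fisher's exact test. No other sensitivity analysis is named in the article.

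**The concern.** A sensitivity analysis should vary an assumption behind the main result and keep the comparison itself intact. This one changes who is being compared. Every decliner with described follow-up chose the inpatient setting, so in any two-group re-run all of them land on one side while the day-case side stays as randomised. They have no allocation, so they cannot be analysed by intention to treat.

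The outcomes most exposed are those that preference can influence directly in an unblinded trial: satisfaction, quality of life, and costs including sick leave. The satisfaction survey asks patients about the group they were allocated to. Decliners were not allocated; they received what they asked for.

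What is at stake is interpretation. Agreement with the main result could be offered as reassurance, or disagreement as doubt, when either could come from self-selection.

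**Working it through.** **Inputs from the recruitment section.** The stated aim of the calculation is: "To establish equivalence in postoperative mean air conduction of 5 dB (standard deviation 10) between the day-case and the inpatient group". The type I error rate is 0.05 (sidedness not stated), the power is 80%, and the result is 51 per group. For withdrawal, "5 more participants than needed will be recruited per group". The total is 112 and the assumed participation rate is 75%.

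**The plan's own figure.** With one-sided alpha 0.05, a 5 dB limit, SD 10 and true difference 0, the normal formula gives n = 2 × (1.645 + 0.842)² × 10² / 5² = 49.5, so 50 per group. By the t distribution, 50 gives 79.9% power and 51 gives 80.6%, so 51 is reproduced. Then 51 + 5 = 56 per group and 2 × 56 = 112. Whether a one-sided calculation suits an equivalence aim is a separate question; only the 56 per group matters here.

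**How many decliners there could be.** 112 / 0.75 = 149.3 patients approached, and 149.3 − 112 = about 37 non-participants. This is a ceiling: it counts refusal for any reason and supposes that everyone agrees to follow-up.

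**Effect on the comparison.** If m decliners are pooled with 56 randomised inpatients, their share is w = m / (56 + m). If their mean air conduction differs from that of randomised inpatients by d dB, the inpatient mean, and so the between-group difference, moves by w × d. The article gives neither m nor d, so both are assumed ranges.

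| Share of 37 followed | m | Inpatient side | w (shift per 1 dB) | Shift, d = 2 dB | d = 5 dB | d = 10 dB |
|---|---|---|---|---|---|---|
| 25% | 9 | 65 | 0.14 | 0.28 | 0.69 | 1.38 |
| 50% | 18 | 74 | 0.24 | 0.49 | 1.22 | 2.43 |
| 75% | 28 | 84 | 0.33 | 0.67 | 1.67 | 3.33 |
| 100% | 37 | 93 | 0.40 | 0.80 | 1.99 | 3.98 |

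**Apparent precision.** At SD 10 the standard error of the difference is 10 × √(1/56 + 1/56) = 1.89 dB for the randomised groups and 10 × √(1/56 + 1/93) = 1.69 dB at the ceiling. The interval narrows while bias enters.

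**Illustration.** Suppose the true randomised difference is 5 dB, equivalence is declared when a 90% interval lies within ±5 dB (an assumed rule), and decliners differ by 5 dB in the direction that narrows the gap. The chance of declaring equivalence in the pooled analysis rises from 5% to 10%, 17%, 25% and 32% down the rows of the table. A difference in the other direction would lower it.

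**The case against.** The strongest reply is that pooling is inferred. The article says that the data will be used, not that they will be merged with the inpatient arm or compared without adjustment. A separate description would fit the words and would be harmless. This stands as a limit. Even so, a sensitivity analysis of a two-group result ordinarily means re-running that comparison, and the article names only unadjusted tests beside it. If a separate report was meant, one sentence would settle it.

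Four stronger readings are tempting, and the article does not support them.

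- **That the randomised comparison is broken.** It is not. The main analyses remain intention-to-treat, and no decision rule in the article depends on the sensitivity analysis.
- **That 40% of the inpatient side will be self-selected.** That is the ceiling. No mechanism is given by which wanting an overnight stay would change thresholds after the same operation, so the dB differences are purely illustrative.
- **That the shift can be judged against the largest observed difference still compatible with equivalence.** That limit depends on sample size and interval. It is 5 − 1.645 × 10 × √(2/51) = 1.74 dB for 51 against 51 with a 90% interval, but 5 − 1.645 × 1.69 = 2.22 dB for 56 against 93. The article specifies 95% intervals, which would lower both. The smaller figure does not apply to the pooled sample.
- **That the trial neglects data missing not at random.** An article may leave such analyses to the full protocol or analysis plan, so their absence here is not a finding.

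Decliners' data also have a proper use. With a quarter of eligible patients expected not to take part, they bear on generalisability.

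**Conclusion.** The point holds in a limited form. The two sections together describe a sensitivity analysis whose extra patients can enter the inpatient side only, by their own choice and without randomisation. If the comparison is re-run with them, it is confounded, conflicts with the intention-to-treat statement and is not evidence of robustness.

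For hearing, the possible distortion is about 0.14 to 0.40 dB per 1 dB of difference between decliners and randomised inpatients, against a 5 dB margin. This rests on 75% participation, 25% to 100% of the 37 being followed, and simple pooling. The effect on satisfaction, quality of life and costs is more plausible but cannot be sized from the article. The flaw is confined to a secondary analysis and is worth correcting because it is stated, avoidable and easily misread.

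**What to change.** In the Statistical analysis section, replace the sensitivity-analysis sentence with text to this effect:

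- Patients who declined randomisation and agreed to follow-up are reported as a separate, descriptive, non-randomised cohort, to inform generalisability. Their data are not pooled with the randomised inpatient arm.
- Sensitivity analyses of the primary outcome use randomised patients only, for example a complete-case analysis alongside multiple imputation.

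The cost is a change of wording and slightly more analysis work. Data collection stays as it is. The article reports that the trial is still recruiting, so the change can be made before the analysis.

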### Safety reporting, ethics and funding

The study will be conducted according to the principles of the Declaration of Helsinki (Fortaleza, 2013) and in accordance with the Medical Research Involving Human Subjects Act (WMO). The study will be funded by the UMC Utrecht. As such it was peer reviewed by the funding organization. This research protocol was approved by the Institutional Review Board of the UMC Utrecht (NL45219.041.13; version 3, March 2015). The approved research protocol can be found online in the Netherlands Trial Register (www.trialregister.nl): NTR4133, registration date 21^st^ August 2013.

All cases of serious adverse events will be reported to the local Institutional Review Board and adequately followed up. An independent monitor is appointed to check trial quality (completeness of informed consent forms, validity of data, etc.) once a year. All data will be handled confidentially. The data will be analysed anonymously by using a unique patient identification number. The investigator will safeguard the key to the code. The primary source of the data will be paper files, which will be stored in a locked room. The data will be stored on the investigator’s computer as well, which is secured by a password and located in a locked room.

### Trial status

The trial is currently in recruitment phase.

## Discussion/conclusion

Stapes surgery seems to be a surgical procedure that is well suited for day-case treatment as it has proven to be a safe treatment with low complication rates. However, current literature lacks evidence based recommendations supporting day-case stapes surgery. This randomized controlled trial allows for a comparison between day-case and inpatient stapes surgery to investigate the hypothesis that day-case stapes surgery is associated with a higher QoL and higher cost-effectiveness, while maintaining equal hearing results, compared to inpatient stapes surgery. This is the first high quality trial evaluating and quantifying the benefits of day-case stapes surgery for patients with otosclerosis.

## Abbreviations

ENT: ear, nose and throat
QoL: quality of life
TBQ: tinnitus burden questionnaire
UMC Utrecht: University Medical Center Utrecht
VBQ: vertigo burden questionnaire
WMO: medical research involving human subjects act
